## Abstract

**Background:**

Medication adherence refers to whether a patient takes medication according to the frequency prescribed, or continues to take a prescribed medication. Inadequate adherence to medication may cause alterations in risk-benefit ratios, resulting in reduced benefits, increased risks or both, and is significantly associated with adverse clinical outcomes and higher healthcare costs. We aim to examine the effect of a computer generated short message service (SMS) reminder in improving medication adherence, and inhibiting the aromatisation process amongst breast cancer women receiving oral aromatase inhibitor therapy.

**Methods/Design:**

In this randomised controlled trial, eligible patients will be equally allocated to receive either SMS reminder or standard care. The former receives weekly SMS reminder to take medication while the latter does not receive any. The primary endpoint of medication adherence at 1-year is assessed using the Simplified Medication Adherence Questionnaire, and compared using the χ^2^ test. Adjustment for baseline covariate and potential confounders will be made using the logistic regression. Secondary outcomes involving estrone and androstenedione levels will be compared using the analysis of covariance, whereas the estradiol levels (< 18.4 pmol/L versus ≥18.4 pmol/L) will be compared using the χ^2^ test, and the logistic regression. Further, the assessment of knowledge, attitude, behaviour, and barriers and facilitating factors of medication adherence will be made via logistic regression.

**Discussion:**

This will be the first study to evaluate short-term clinical outcomes from SMS reminder for breast cancer patients on aromatase inhibitor therapy. Random allocation to SMS reminder or control arm ensures that patients in both arms will be comparable with respect to demographic and clinical characteristics, and any difference in outcomes can be attributed to the intervention. Participants are not blinded to the assignment of intervention, thus there may be potential for bias in outcome assessments.

**Trial registration:**

NCT02524548. Retrospectively registered on 17 August 2015.

## Background

Medication adherence typically refers to whether a patient takes medication according to the frequency prescribed, or continues to take a prescribed medication [1]. The World Health Organisation defines medication adherence to long-term therapy as “the extent to which a person’s behaviour - taking medication, following a diet, and/or executing lifestyle changes, corresponds with agreed recommendations from a health care provider” [2]. Accruing evidences show that inadequate medication compliance can cause alterations in benefit/risk ratios, resulting in reduced benefits, increased risks or both [3, 4]. Medication non-adherence is significantly associated with adverse clinical outcomes and higher healthcare costs [5].

### Aromatase inhibitor and breast cancer risk and recurrence

Breast cancer is the leading type of cancer affecting women, and it was estimated that worldwide over 508,000 women died of this condition in 2011 [6]. In Singapore, it is also the primary cause of death for women from 2011 to 2015 [7]. Besides, a total of 9634 new cases of breast cancer were diagnosed in the same period, accounting for 29.1% of incident cancers in females and making it the most common cancer among women [7].

Estrogen promotes the growth and survival of normal and cancerous breast epithelial cells by binding and activating the estrogen receptor (ER). The activated receptor in turn binds to gene promoters in the nucleus and activates many other genes responsible for cell division, inhibition of cell death, new blood vessel formation and protease activity [8]. Thus, hormone therapy, which is a form of systemic therapy, is recommended for women with hormone receptor-positive breast cancer. Aromatase inhibitor (AI), a commonly prescribed hormonal therapy for early stage breast cancer, interferes with the body’s ability to produce estrogen from androgens by suppressing the aromatase enzyme activity. Research has shown that women treated with adjuvant hormone therapy for early-stage ER positive breast cancer gain at least 5 more years due to the treatment. However, it has been reported that patients could suffer from serious side effects of the hormone therapy [9].

Key et al. demonstrated a significant association between breast cancer risk and circulating estrogens in postmenopausal women [10]. Estrogen is the main stimulant in the development and growth of breast cancer, [11] and higher endogenous estrogen level has been found to be associated with elevated breast cancer risk. Tamoxifen has been successfully used for treating ER positive breast cancer for the past three decades. More recently, AI has been demonstrated to provide a significant reduction in breast cancer recurrence in post-menopausal women [4]. Following menopause, aromatase in fat and muscle may be responsible for much of the circulating estrogen. In highly estrogen-sensitive tissues such as the breast, uterus, vagina, bone, brain, heart and blood vessels, it provides local estrogen in an autocrine fashion. The aromatase gene promoter in breast tissue is less sensitive than the gene promoter in the ovary due to fluctuations in luteinising hormone but much more sensitive to increases in inflammatory cytokines, which increases with age. In particular, breast tissue inflammatory cytokines increase with proliferative breast disease and breast cancer [8].

A prospective, multi-centre, non-interventional study reported significant improvements in long-term quality of life of postmenopausal Chinese patients with hormone-receptor-positive early-stage breast cancer after starting treatment with AI [12]. A recent meta-analysis also showed the superiority of AI as an adjuvant hormonal therapy in improving the disease-free and overall survival of postmenopausal ER-positive breast cancer as compared to tamoxifen [13]. In another clinical trial, researchers have suggested that improvement in overall survival (hazard ratio 0.78; 95% CI 0.62 to 0.98) was seen among premenopausal women with the use of exemestane plus ovarian suppression as compared to tamoxifen users [14].

However, adverse events include hot flushes, vaginal dryness, loss of libido, fatigue, arthralgia, joint stiffness and loss of bone mineral density with subsequent increased risk of fracture [8, 15]. Also, as the treatment of AI is long-term, medication adherence is an issue of concern, with a proportion of women stopping before completing the full treatment, while others not taking a daily tablet regularly [16, 17]. Its adherence rate has been shown to decline over time from 78 to 86% in the first year, and reaching 62 to 79% by Year 3 [17]. A recent nested case-control study showed that non-adherence to oral endocrine therapy was significantly associated with worse breast cancer survival (OR 4.07; 95% CI 3.27–5.06) [18].

### Intervention to improve medication adherence

Recent reviews have shown that although various behavioural, educational, integrated care and self-management risk communication interventions have been implemented to improve medication adherence, none of them have shown promising impact [19, 20]. On the other hand, studies have suggested that reminder of any form, such as setting an alarm on a regular daily basis at home, or have family reminding the patient to take medication, have a positive influence on medication adherence in cancer patients [19]. While healthcare institutions sometimes use short message service (SMS) to remind patients of follow-up clinic appointments, mobile technology is seldom implemented to monitor medication adherence until the recent decade [21]. This is a feasible and acceptable form of managing medication which has a high participant satisfaction [22]. Its use has been shown to improve medication adherence in cardiovascular disease, diabetes, HIV, oral contraception, asthma, as well as oncology patients with chronic conditions [22, 23]. As mobile phone ownership continues to increase, there is a great potential to utilise this technology to overcome adherence barriers and optimise therapeutic effects [24].

### Barriers and facilitating factors influencing medication adherence

Malcolm et al. identified cost, side-effects, transportation, lack of reimbursement for the medication and inefficient patient-physician communication as barriers to medication adherence [25]. Medication-taking behaviour has been shown to be influenced by a patient’s belief and his/her trust in the physician who prescribes the medication [26]. Also, non-adherence to endocrine therapy might be due to patients’ response to the AI therapy and its associated side effects such as arthralgia [27]. Besides, it has been shown that nonadherence to medications for chronic diseases prior to hormonal therapy was associated with more severe nonadherence to oral hormonal therapy in patients with breast cancer [28] A cross-sectional study comprising mostly White women showed that survivors who perceived that their pain made taking AIs difficult or that the AI treatment lasted too long were likely to be non-adherent, as assessed by the Health Beliefs Scale Items and Scale Properties [29]. In contrast, a systematic review showed that taking more medications at baseline, referral to an oncologist, and being diagnosed at earlier times were positively associated with adherence and/or persistence [16]. Thus, in non-adherent patients, it is desirable to understand their attitude and perception towards medication taking.

Cancer treatment adherence plays a crucial role in optimising health outcomes while medication non-adherence is associated with decreased survival, higher recurrences and increased healthcare costs. Hsieh et al. reported that interruption and non-adherence to long-term adjuvant hormone therapy was associated with increased mortality in breast cancer women [30]. Treatment non-adherence to adjuvant hormonal therapy was found to be associated with increased all-cause mortality amongst Asian breast cancer women. Moreover, a greater impact of non-adherence on mortality was especially found in the younger breast cancer population [30].

Implementing innovative technology to tackle the problem of non-adherence and understanding its barriers will provide scientific evidence for clinical decision making and improve health outcomes. We thus propose to examine the effect of a computer automated SMS reminder in improving medication adherence amongst breast cancer women receiving oral AI therapy.

### Study objectives

The primary objective is to evaluate whether SMS reminder improves medication adherence as compared to standard care (control) amongst breast cancer women who have been receiving adjuvant endocrine therapy for at least 1 year, and are continuing to receive adjuvant AI therapy for at least 1 more year.

The secondary objectives are to examine whether SMS reminder improves the inhibition of aromatisation process of patients receiving AI therapy. We postulate that at 1-year, there will beLower estrone and estradiol levels in the SMS reminder group as compared to the control.Higher androstenedione level in the SMS reminder group as compared to the control.

Tertiary objectives includeAssessing the impact of SMS reminder on the improvement in knowledge, attitude and behaviour towards medication compliance.Identifying barriers and facilitating factors for medication adherence.

## Methods/Design

### Study design

This is an open-label, multi-centre prospective randomised controlled trial of SMS reminder versus standard care to investigate whether SMS reminder improves adherence to oral AI therapy in breast cancer women at 1-year follow-up. A total of 280 breast cancer women will be recruited from the National University Cancer Institute, Singapore and the Ng Teng Fong General Hospital, Singapore. Eligible participants will receive financial compensation for each study visit in an amount within the guidelines of the ethics review board.

### Inclusion criteria

Women who have been receiving adjuvant endocrine therapy for at least 1 year, and are continuing to receive adjuvant AI therapy for at least 1 more year.Aged 21 to 80 years.Have cellular phone that can receive text messages.Singaporean or permanent resident who is currently residing in Singapore.Able to give informed consent.

### Exclusion criteria

Unable or not willing to comply with study procedures.

### Study intervention

A systematic review involving HIV patients found weekly reminders to significantly improve the percentage of achieving 90% adherence, while daily reminders showed no improvement [31]. Thus, we propose to send weekly SMS reminders on the first working day of each week, that is, at 9:00 AM each Monday morning from a tablet via an automated messaging system, throughout the 1-year follow-up period for the intervention group. A screen shot of the message sent is shown in Fig. 1.

**Fig. 1 Fig1:**
[figure not shown]
SMS reminder from the automated messaging system

The message includes information on patient’s name, date, hospital, medication and frequency of oral AI therapy. In order to cater to the multi-ethnic study population, the message is translated to Mandarin or Malay. If a patient is not proficient in English, the messages will be sent using her preferred language. The control group will not receive any message. Regardless of the randomised allocation, all patients will be given a log for the next 6 months to record whether they have received the message (for the intervention group) or taken the pills according to instruction. The log will be recalled on the subsequent visit and a new log will be distributed to patients for recording the information for the subsequent 6 months. This log will be returned to the study coordinator at the end of the study.

### Randomisation procedure

All eligible patients who have provided informed consent will be randomised to receive either SMS reminder or standard care in a 1:1 ratio. Balanced permuted block randomisation will be implemented with varying block sizes, stratified by centre. Allocation concealment will be ensured, as the randomisation allocation, generated by the responsible statistician, will not be released to the research coordinator until the patient has been recruited into the trial by means of a central telephone call upon meeting the eligibility criteria. The study flow chart is shown in Fig. 2.

**Fig. 2 Fig2:**
[figure not shown]
Study flow chart

### Data collection

Three questionnaires will be administered via face-to-face interview by the Research coordinator. The Simplified Medication Adherence Questionnaire (SMAQ) is a validated 6-item questionnaire which measures adherence [32]. Non-compliance is defined if a patient responds to any of items 1 to 4 with a non-adherence answer; and if the patient has skipped more than two doses during the last week or has not taken medication for more than two complete days during the last visit. In addition, information on knowledge, attitude and behaviour towards medication taking will be elicited via the Beliefs about Medicines Questionnaire (BMQ) [33] and the Adherence Starts with Knowledge (ASK-12) questionnaire [34].

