### Follow-up and assessments

The assessments and follow-up schedule (with a window period of ±2 months) are summarised in Table 1.

**Table 1 Tab1:** Summary of study procedures and schedule

Study procedures	Visit 1	Visit 2	Visit 3
	Screening/Baseline	Month 6	Month 12
Informed consent	x		
Assess eligibility	x		
SMAQ	x	x	x
BMQ, ASK-12	x		x
Prescription data	x	x	x
Pill count and refill data		x	x
Estrone, estradiol and androstenedione assays	x		x
UPIRTSO event		x	x
Patient log of daily pill taken and weekly SMS		x	x
^a^Check receipt of SMS	x	x	x

^a^Research coordinator will verbally check the status of SMS receipt at each clinic visit

The patients will be followed up half yearly. The SMAQ will be administered at each visit, while the BMQ and ASK-12 questionnaires will be administered at baseline and 1-year. The hormone assays of estrone, estradiol and androstenedione will also be performed at baseline and 1-year.

This trial does not involve any experimental treatment and thus poses no additional risks to patients. Nevertheless, at each follow-up visit, the research coordinator will record any symptom or event that a patient may have experienced that is considered as UPIRTSO (Unanticipated Problems Involving Risks to Subjects and Others) event. These events will be monitored closely using a log book.

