### Statistical considerations

#### Sample size

The sample size is estimated based on the primary endpoint of medication adherence (as measured via SMAQ) at 1-year. Assuming that the proportion of medication adherence in the intervention and control groups are 80 and 60% respectively, [17] then based on a 5% significance level and a power of 90%, a minimum sample of 240 subjects (i.e. 120 per group) will be required. Further assuming an attrition rate of 10%, the overall trial size is 280.

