### Assessing medication adherence

There are different ways of assessing medication compliance. Patient self-reporting relies mainly on a patient’s recall, and is susceptible to bias. Pill count has also been shown to be unreliable especially if patients fail to return the bottles or dumped the pills before the count [35]. Medication possession ratio is commonly used for claims-based adherence measurement. However, it overestimates the true adherence rate particularly when a patient receives an early refill of the medication. The proportion of days covered (PDC), a recent method for calculating adherence, avoids double counting when refills overlap or when oversupply of medication exists [36]. However, it ignores instances when patients refill their prescriptions before finishing the drug.

In a further sub-study, we will compare the four different measures of adherence, to determine which of these provide a more meaningful or reliable information in the local context based on different performance indicators such as the sensitivity, specificity and kappa statistics using PDC as the gold standard. The percentages of adherence between the different measures will be compared via the McNemar’s test.

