Studies on breast cancer have demonstrated that patients commonly reported suffering from physical and psychological inconvenience due to AI therapies [41]. As compared to women without a history of cancer, breast cancer patients, reported significantly higher odds of new onset of forgetfulness, difficulty in concentrating, hair loss and numbness or tingling in the extremities after the first 6 months of AI therapy, with odds ratio ranging between 2 to 4 folds [41]. A German study also showed that age contributed to the difference in medication adherence amongst breast cancer women who were treated with AI [42]. It suggested that patients aged over 70 years exhibited a 25% reduction in risk of treatment discontinuation as compared to younger patients. However, a literature review discussing poor adherence with hormonal therapy among women with breast cancer disagreed with the notion that non-adherence could be due to older age (≥55 years). It reported that other reasons for hormonal therapy non-adherence could be due to patient’s behaviour, treatment toxicity, cost of health care or medications, and comorbidities [43]. Also, it has been further suggested that medication compliance may be improved if financial barriers were removed [43]. Meanwhile, other researchers have identified socio-demographic and clinical characteristics to be associated with medication beliefs about AI such as concern, perceived necessity of taking the drug to improve one’s health, and cancer/health worry amongst postmenopausal women [44].

This trial has several strengths as well as limitations. This will be the first study to evaluate short-term clinical outcomes from SMS reminder for breast cancer patients on AI therapy. Random allocation to SMS reminder or control arm ensures that patients in both arms will be comparable with respect to demographic and clinical characteristics, and any difference in outcomes can be attributed to the intervention. However, participants are not blinded to the assignment of intervention, thus there may be potential for bias in outcome assessments.

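### The between-arm adherence comparison rests on interviewer-administered self-report in an open-label trial, while refill-based PDC is compared with other measures but not between arms

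*Protocol article*

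**What the plan says.** **Design and primary endpoint.** Under Study design: "This is an open-label, multi-centre prospective randomised controlled trial of SMS reminder versus standard care". Under Sample size: "The sample size is estimated based on the primary endpoint of medication adherence (as measured via SMAQ) at 1-year". The Abstract also names the SMAQ as the primary measure.

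**Who asks, and what they know.** Under Data collection: "Three questionnaires will be administered via face-to-face interview by the Research coordinator". Under Randomisation procedure, the allocation "will not be released to the research coordinator until the patient has been recruited into the trial", so the coordinator is blind only up to that moment. The footnote to Table 1 adds: "Research coordinator will verbally check the status of SMS receipt at each clinic visit".

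**The article's view of the measures.** The section Assessing medication adherence says that self-report depends on recall and is open to bias. It also criticises pill count, the medication possession ratio and PDC. It then describes a sub-study comparing four measures by "sensitivity, specificity and kappa statistics using PDC as the gold standard", with McNemar's test for the percentages adherent.

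**What is collected and what is compared.** Table 1 schedules prescription data at all three visits and "Pill count and refill data" at Months 6 and 12. The section Statistical analysis plan lists these between-arm comparisons: adherence at 1 year, estrone, androstenedione, estradiol, and the knowledge, attitude, behaviour, barrier and facilitator items.

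**The interpretation offered.** The Abstract and the Discussion both say that randomisation makes the arms comparable, so that differences in outcome may be ascribed to the intervention. Both then concede that "participants are not blinded to the assignment of intervention, thus there may be potential for bias in outcome assessments".

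**The concern.** The intervention is a weekly message about taking a tablet, and the outcome is the woman's own account of whether she took it. The message can therefore change the answer without changing the behaviour, and it reaches one arm only. Randomisation balances the patients but not the way they report afterwards. The interviewer also knows, or can easily learn, which arm the woman is in.

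At stake is the reading of a positive primary result. The trial will hold refill data on the same women that do not depend on what they tell the interviewer. As the analyses are stated, those data are not used to see whether a SMAQ difference is accompanied by a difference in medication obtained.

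**Working it through.** **1. The plan's own figure.** Inputs from Sample size: 80% v 60%, 5% significance (two-sided, from Statistical analysis plan), 90% power. With the pooled mean 0.70:

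n = [1.960·√(2·0.70·0.30) + 1.282·√(0.80·0.20 + 0.60·0.40)]² / 0.20² = 108.2, so 109 per arm.

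With continuity correction: (108.2/4)·[1 + √(1 + 4/(108.2·0.20))]² = 118.0, or 119 per arm when 109 is entered as n. That is 238 in total, which agrees with the stated 240. The sample size is not in dispute.

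**2. Which measures are compared between arms.**

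| Measure | Collected in both arms | Depends on the patient's account | Compared between arms in the stated analyses |
|---|---|---|---|
| SMAQ | Baseline, Months 6 and 12 | Yes | Yes (primary) |
| Prescription and refill data (source of PDC) | Prescription at all visits; refill at Months 6 and 12 | No | No; sub-study reference only |
| Pill count | Months 6 and 12 | Partly (she must bring the pills back) | No |
| Hormone assays | Baseline, Month 12 | No | Yes (secondary) |

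Sensitivity, specificity, kappa and McNemar's test all compare one measure with another in the same patients. None estimates the effect of SMS.

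**3. How much differential reporting could matter (illustration).** Assumptions, none from the article: true adherence is 60% in both arms (the article's control rate), a share q of non-adherent SMS-arm women report adherence, and no control woman does. Analysed number: 280 × 0.90 = 252, or 126 per arm.

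Observed SMS-arm adherence: p₁ = 0.60 + 0.40·q. Control: p₂ = 0.60. With p̄ their mean,

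SE₀ = √(2·p̄(1−p̄)/126), SE₁ = √{[p₁(1−p₁) + p₂(1−p₂)]/126},

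chance of a significant benefit = Φ[(p₁ − p₂ − 1.960·SE₀)/SE₁].

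| q | p₁ | SE₀ | SE₁ | Argument of Φ | Chance of false benefit |
|---|---|---|---|---|---|
| 0 | 60% | 0.0617 | 0.0617 | −1.960 | 2.5% |
| 0.10 | 64% | 0.0612 | 0.0611 | −1.307 | 9.6% |
| 0.20 | 68% | 0.0605 | 0.0603 | −0.639 | 26.1% |
| 0.25 | 70% | 0.0601 | 0.0598 | −0.298 | 38.3% |

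At 120 per arm the last three are 9.3%, 25.1% and 36.8%. At q = 0.50 the observed rates would be 80% v 60%, the whole planned effect.

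Only the difference in over-reporting between arms matters. If q were 0.20 in both arms, both would show 68% and the chance would return to 2.5%.

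**4. Whether a PDC comparison would be informative at the planned size.** The same formula with 120 per arm gives power of 93% for 80% v 60%, 70% for 75% v 60%, and 37% for 70% v 60%. Only the first pair is the article's, and it was set for the SMAQ; the others are assumptions. At the planned effect no extra patients are needed.

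**The case against.** **Objective between-arm evidence already exists.** Estrone, estradiol and androstenedione are pre-specified, measured at baseline and 1 year, and compared with baseline adjustment. This stands. A reader might infer that a positive SMAQ result could not be told apart from reporting bias at all. The article does not support that, because a concordant hormone result would speak against it. The assays nonetheless register aromatase inhibition, not pill-taking.

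**PDC is not clean either.** The article lists its weakness and calls pill count unreliable, and PDC is the reference standard only within a sub-study meant to learn which measure is most useful locally. This also stands. PDC records possession, whereas the SMAQ asks about missed doses, and a reminder could reduce missed doses without altering refills. A reader might therefore want a rule that benefit is claimed only if PDC agrees. The article gives no ground for that, and such a rule could deny a real effect on taking.

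**Silence is not exclusion.** The article is condensed, the full protocol and analysis plan are not shown, and nothing says that PDC will not be compared between arms. A reader might infer that it has been ruled out, but that goes too far. What can be said is that the article sets out its objectives, its between-arm analyses and a separate sub-study, and gives PDC an explicit role only in the last.

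**The size is hypothetical.** Over-reporting shares of 10% to 25% have no source in the article. All women keep a pill log whatever their arm, so controls are also cued and may over-report too.

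**Coordinator knowledge and visit order are partly inferred.** The article says outright only that participants are unblinded. That the coordinator is unblinded follows from the release of the allocation and the SMS-receipt check. Nothing says that SMS receipt is asked before the SMAQ. Replacing the interview with self-completion would have its own cost in women aged up to 80, some not proficient in English.

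**The limitation is disclosed.** It is, directly after the attribution sentence, but no mitigation is stated.

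**Conclusion.** The point holds in a limited form. The primary adherence comparison uses self-report taken face to face by a coordinator who receives the allocation, in an open-label trial whose own text regards self-report as prone to bias. Refill-based PDC can be derived from data already scheduled in both arms, but in the stated analyses it is set only against other measures. The hormone assays are the only objective between-arm outcomes, and they bear on adherence indirectly.

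The false-benefit figures show sensitivity and do not forecast what will happen. They rest on equal true adherence of 60%, 126 analysed per arm, and over-reporting in the SMS arm alone. The direction of the concern is well founded; its size is unknown. The trial remains valid, and the primary endpoint need not be replaced.

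**What to change.** 1. **Add a supportive secondary analysis** to the Statistical analysis plan section: an intention-to-treat comparison between arms of 12-month PDC, as a mean and as the proportion above a cut-off fixed in advance, with the same type of model as for the SMAQ. Interpret the SMAQ result alongside PDC and the hormone results, without making PDC a formal condition for claiming benefit.
2. **Fix the visit order:** complete the SMAQ before the log is collected and before SMS receipt is checked.
3. **Qualify the attribution statement** in the Abstract and the Discussion: randomisation supports comparability of the patients, but a difference in self-reported adherence may partly reflect reporting.

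The cost is a little more analysis work, one visit instruction and some wording. No new data or patients are needed. The limitation to state is that PDC measures possession rather than ingestion, so a SMAQ effect without a PDC effect would be ambiguous and would not by itself disprove benefit.
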